#### Secondary outcomes

***Pill burden:***Frequency and total number of daily medications, collected from medical records and confirmed during patient interviews. Pill burden was operationalised as a simple count of medications combined with their frequency of administration per day. This measure did not account for dosage forms or specific administration instructions.***Deprescribing outcome:*** Total medications successfully discontinued, dose-reduced, substituted, or restarted after intervention (at 6-month follow-up), categorised by targeted pharmacological drug class.***Health-related quality of life (HRQoL)****:* This will be measured using the self-administered Kidney Disease Quality of Life (KDQOL™) questionnaire (Hays et al., 1994).***Treatment burden:*** This will be assessed using the Treatment Burden Questionnaire (TBQ) (Tran et al., 2014).***Medication adherence****:* Assessed using the Adherence to Refills and Medications Scale (ARMS), a validated self-administered adherence measuring tool (Kripalani et al., 2009). Both English and Arabic versions of the tool are available for use in patients with chronic diseases (Alammari et al., 2021; Kripalani et al., 2009; Zidan et al., 2018).***Hospitalizations and emergency department (ED) visits:*** Total number of hospitalisations and ED visits six months after the intervention. This will be extracted from medical records (CERNER).***Cost–benefit and cost-savings:*** The return on investment in the proposed deprescribing intervention will be measured through cost–benefit analysis, considering cost-savings from drug use, hospitalisations, and ED visits compared to intervention costs.***Unanticipated adverse events:*** Withdrawal symptoms (e.g. dyspepsia after stopping PPIs) or the need for drug re-initiation may be encountered in some cases. Each class of medications has different expected withdrawal symptoms. These or any other unanticipated events will be documented and reported to MRC-IRB as per IRB SOP-09.

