**Methods::**

This randomised controlled trial will be conducted at ambulatory dialysis centres, with an internal pilot to assess the feasibility of recruitment, intervention implementation, and safety measures. Patients will be randomised to usual care or an intervention group where a clinical pharmacist, in collaboration with a multidisciplinary healthcare team, will deliver a structured deprescribing intervention, including periodic monitoring over six months. Outcomes will be measured at baseline, three, and six months. The primary outcome is the proportion of patients with at least one potentially inappropriate medication (PIM). Secondary outcomes include pill burden, treatment burden, hospitalisations, emergency department visits, quality of life, and adherence. A cost–benefit analysis will also be performed. A total of 250 patients provides 90% power to detect a 50% reduction in PIM prevalence (α = 0.05). The statistical analysis will be based on the intention-to-treat principle, using mixed-effects models to account for repeated measures.

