### Study groups

The study comprises two groups: (1) Control arm: Patients who receive usual (i.e. standard) ambulatory care. This entails monthly medication reviews conducted as part of routine care, mainly by the nephrologist and in-charge nurses. Moreover, any issues highlighted by the patients or the care team are addressed by the attending physician or referred for necessary consultations. The pharmacist's role in these rotations is limited and occasional, with limited MDT discussions including the patient's medications. Importantly, the setting is no different than other HD and clinic settings where usually the changes of the medications are subject to present complaints or apparent health problems; (2) Intervention arm: Patients who receive a structured deprescribing intervention delivered by the multidisciplinary team during their patient daycare visits at the centre.

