### Deprescribing intervention and workflow

The proposed deprescribing workflow consists of the following stages:
Patient assessment: Upon recruitment, the patient’s information is collected through participant interviews and electronic medical records (via Cerner). These include sociodemographic, clinical, and medication information. Additionally, patients complete self-reported questionnaires to assess medication adherence, treatment burden, and quality of life.Deprescribing plan development: For patients in the intervention group, the clinical pharmacist highlights the potentially problematic medications, drafts a deprescribing plan for each, consult the multidisciplinary team and the relevant specialists, and documents in the patient’s medical records. The potentially problematic medications are identified through the Medication Appropriateness Index (MAI) tool, and the deprescribing plans are drafted using deprescribing algorithms adapted from evidence-based deprescribing guidelines in the CKD setting (Zidan et al., 2025). Validation of these algorithms was conducted through input from an expert panel and piloted during the pilot RCT. The results of the validation and piloting are not yet published. The intervention targets all PIMs as we intend to provide a holistic approach. Prioritising the deprescribing plans is based on patient safety and medication properties. Only one medication is targeted per deprescribing cycle, unless deemed clinically appropriate. These are decided on case-by-case basis during the MDT-CKD meetings.Implementation and monitoring of the deprescribing intervention: The team implements and monitors the approved deprescribing plan during the patient’s appointments at the centre or through follow-up phone calls, as applicable. The team periodically reviews the intervention’s progress, discussing results and addressing any issues to take corrective actions. Monitoring protocols are tailored per medication class as per the clinical guidelines.Deprescribing plan finalisation: During subsequent appointments, the medication plan is reconciled and discussed with the patient. Patients are provided with a deprescribing card, containing updated medication information to ensure clear communication and adherence to the revised regimen.Post-deprescribing follow-up: For each deprescribing plan, the MDT-CKD clinical pharmacist conducts three follow-up interviews or phone calls with the patients on days 2, 7, and 28 post-deprescribing. These follow-ups are designed to monitor late-onset withdrawal symptoms and to address any questions or concerns raised by the patient. Any changes to the patient’s medication regimen are documented and discussed with the multidisciplinary team to ensure appropriate management.Documentation: All deprescribing processes and decisions related to each medication are documented in the participant’s medical records. For process evaluation, a checklist detailing each step of the deprescribing process is completed for every participant to ensure the fidelity of the intervention.

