### Outcome measures

Outcomes will be assessed at different time points (baseline, 3, and 6 months) and compared between the two participant groups.

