#### Detailed analyses approach

For all analyses, differences between treatment groups will be reported with 95% confidence intervals, and statistical significance will be assessed at the two-sided 0.05 level.
Analysis of PIMs (primary outcome) between groups at 6 months will be performed using Poisson regression with adjustment of baseline values, age, comorbidities, and dialysis group. Secondary outcomes will be analyzed similarly, using either ordinary least squares or Poisson regression, as appropriate.Outcomes with repeated measures at 3 and 6 months, including the primary outcome, will be analyzed using mixed-effects models to account for correlated measurements within individuals over time. To assess differences between the two treatment groups, general linear models will include fixed effects for the treatment group, time point, and the interaction between the treatment group and the time point. Treatment effects will be reported separately at 6 months post-randomisation, regardless of the significance of the interaction term.For continuous outcomes, linear regression adjusted for baseline will be used without data transformations. Estimates of the treatment effect will be reported as mean differences in the change from baseline to 6 months between the intervention and control groups. For ordinal categorical outcomes, treatment effect estimates will be reported as proportional odds ratios for the intervention group compared with the control group using logistic regression. For nominal categorial (i.e. count) outcomes, treatment effects will be reported as rate ratios for the intervention group compared with the control group.Efforts will be made to minimise missing data. In case of encountering expected missing data, these will be documented and the reasons for missingness will be explored to enable the researchers to determine the proper imputation mechanism to estimate the missing values.

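### Hospitalisations and ED visits are counted from a start date that controls do not have, and the only count model named for them is Poisson, whose standard errors are too small if the counts are overdispersed

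*Protocol article*

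**What the plan says.** Under Secondary outcomes, the protocol article defines hospital use as "Total number of hospitalisations and ED visits six months after the intervention", taken from the electronic medical record.

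Other sections bear on when that window starts:
- Study groups describes the control arm as "Patients who receive usual (i.e. standard) ambulatory care".
- The Abstract describes the intervention as "including periodic monitoring over six months".
- Deprescribing intervention and workflow says "Only one medication is targeted per deprescribing cycle, unless deemed clinically appropriate". It schedules follow-up contacts at days 2, 7 and 28 for each plan.
- Outcome measures says "Outcomes will be assessed at different time points (baseline, 3, and 6 months) and compared between the two participant groups".
- Detailed analyses approach says "Treatment effects will be reported separately at 6 months post-randomisation, regardless of the significance of the interaction term".

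On the model, Detailed analyses approach says "Secondary outcomes will be analyzed similarly, using either ordinary least squares or Poisson regression, as appropriate". It assigns mixed-effects models to outcomes measured repeatedly at 3 and 6 months, and rate ratios to count outcomes. The Statistical analysis plan section expects some withdrawal and death. The Economic analysis plan takes avoided ED visits and hospitalisations as the cost-avoidance part of the benefit, and charges any increase to the programme.

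**The concern.** A comparison of event counts between randomised arms needs the same clock in both. A clock that starts after the intervention has no counterpart under usual care. In the intervention arm it could start at the first plan, at the last plan or at the end of the programme. Someone extracting events from the record could apply different start dates by arm and still follow the text. A clock that starts once a plan is complete would also leave out admissions during drug withdrawal, which is when the Risk mitigation strategy looks for harm.

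The second issue is the model. Admissions and ED visits often concentrate in a minority of patients, so the variance may well exceed the mean. Model-based Poisson standard errors are then too small. The outcome is defined as a single total per patient, so it is not clear that the mixed models for repeated measures would absorb the extra variation.

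The third and lesser issue is that a rate ratio needs a time base, and none is stated although early exits are expected.

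At stake are the safety reading, the claim of fewer admissions, and the cost-avoidance term. The window affects all three. The standard errors affect only the tests and intervals, not the point estimate of cost avoided.

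**Working it through.** **Window.** Possible start dates compared:

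| Start of the six months | Defined for controls? | Fits the 3- and 6-month schedule? | Covers the withdrawal period? |
|---|---|---|---|
| Randomisation | Yes | Yes | Yes |
| First or last completed plan | No | Not in general; varies by patient | Not fully |
| End of the six-month programme | No | No; 6 + 6 = about month 12 | No |

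Only the first row works for both arms, and the outcome definition does not state it.

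**Overdispersion.** The protocol gives no event rate, variance or sample-size figure for these outcomes, so there is nothing of its own to reproduce. The inputs are:
- two-sided α of 0.05 (Detailed analyses approach);
- 125 patients per arm (Sample size);
- variance/mean ratio φ, which is assumed. For a negative binomial count with mean μ and dispersion k, φ = 1 + kμ.

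The true standard error is √φ times the Poisson one. The type I error of a nominal 5% Wald test is 2[1 − Φ(1.96/√φ)].

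| φ | Example (μ, k) | True SE ÷ Poisson SE | 1.96/√φ | Type I error | Simulated |
|---|---|---|---|---|---|
| 1 | 0.5, 0 | 1.00 | 1.96 | 5.0% | 4.75% |
| 1.25 | 0.5, 0.5 | 1.12 | 1.75 | 8.0% | 8.4% |
| 1.5 | 0.5, 1 | 1.22 | 1.60 | 11.0% | 10.6% |
| 2 | 0.5, 2 | 1.41 | 1.39 | 16.6% | 16.7% |
| 3 | 1.0, 2 | 1.73 | 1.13 | 25.8% | 26.2% |

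The simulations used 125 per arm, no treatment effect, no covariates and 4,000 trials per row. At φ = 2 the Poisson standard error is 1 − 1/1.414 = 29% too small. With robust variance, simulated type I error was 5.1–5.2% in 3,000 trials at 112 per arm (φ from 1.5 to 2.6).

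**Time at risk.** Suppose a fraction d of an arm leaves at a uniformly distributed time. Mean follow-up is then 1 − d/2 of the full period. Without an offset, the expected rate ratio under no effect is (1 − d_I/2)/(1 − d_C/2), for intervention (I) and control (C).
- 10% in both arms (the protocol's rate, assumed equal): 0.95/0.95 = 1.00.
- 15% versus 5% (assumed): 0.925/0.975 = 0.949.
- 20% versus 0% (assumed): 0.90/1.00 = 0.90.

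Simulation gave 1.00, 0.95 and 0.90 without the offset, and 1.00 in all three cases with it.

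**The case against.** The strongest reply is that the wording is shorthand for the 6-month visit. All outcomes are scheduled at baseline, 3 and 6 months in both groups, and effects are reported at 6 months post-randomisation. The neighbouring deprescribing outcome uses a similar phrase and adds in brackets that it means the 6-month follow-up. No section mentions follow-up to month 12. This stands as far as intent goes. A reader might infer that the two arms will in fact be counted over different windows, but the documents do not support that. They show only a definition that does not state the window the rest of the text implies.

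On the model, the choice between the two is left to be made as appropriate, rate ratios are promised, and an offset or robust variance is detail that a condensed article may leave to an analysis plan that is not shown. This also stands. A reader might infer that unadjusted Poisson intervals without follow-up time are planned and will be too narrow. The text does not say so, gives no dispersion, and excludes neither remedy. The planned adjustment for baseline value, age, comorbidities and dialysis group would absorb some of the between-patient variation, so the tabulated rates may be high. What remains is that neither named model, in its standard form, suits overdispersed counts.

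Two further points hold. These are secondary outcomes without a multiplicity claim, and the economic sensitivity analyses may cover some uncertainty in event probabilities. Varying those inputs does not, however, repair an event count taken over an undefined window.

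**Conclusion.** The definition of the window should be corrected. Its start date does not exist for controls, is not unique for intervention patients and does not match the post-randomisation time point in the analysis section. It is ambiguous, not shown to be unequal.

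Narrow intervals are a conditional risk. Type I error stays at about 5% with no overdispersion and rises to 8–11% when overdispersion is mild (φ of 1.25 to 1.5), 17% at φ = 2 and 26% at φ = 3. These ratios are assumed and the figures are before covariate adjustment. Overdispersion is likely for hospital use, but the documents cannot confirm it.

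Missing time at risk is a separate and smaller matter. It biases the ratio only when follow-up differs between arms, to about 0.95 under the assumed 15% versus 5% split, and not at all when follow-up is equal.

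The change is worth making because the outcome feeds the benefit-to-cost ratio and the safety reading. The primary analysis is not affected.

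**What to change.** In Secondary outcomes, define the outcome as all hospitalisations and all ED visits from the date of randomisation to month 6, in both arms.

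In Detailed analyses approach, name Poisson regression with robust variance (or negative binomial regression; either will do) with log time at risk as offset. End time at risk only at death, withdrawal of consent to record access, or loss of record coverage. Do not end it when a patient merely stops the programme. Those patients' events remain visible in the record, and dropping them would go against the stated intention-to-treat principle.

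Use the same window for the cost-avoidance calculation.

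The cost is a change of wording. The events are already to be taken from the medical record, so no extra patient visits are needed. Intervals will be somewhat wider if the counts are overdispersed and about the same if they are not.

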#### Pilot stage outcomes

The following outcomes are measured during the ongoing pilot stage:
Recruitment of ≥ 70% of eligible patients.Delivery of ≥ 75% of the intervention components.Retention rate of ≥75% at 6 months for outcome measures.No significant intervention-related safety concerns.

Furthermore, a detailed process evaluation is being conducted in accordance with MRC guidance [23] and will be published separately.

### Data collection instruments

*Data collection form:* An Excel sheet was developed to collect demographic and clinical data and outcome measures. It contains participants’ characteristics, medical history, comorbidities, prescription information, laboratory data, and patient-reported outcomes.*Treatment Burden Questionnaire (TBQ):* The instrument’s responses are rated using a Likert-type scale ranging from 0 (not a problem) to 10 (a big problem). The TBQ global score is calculated by summation of each item score, with a maximum score of 150 points. The scores are further categorised as low burden (0–50), moderate burden (51–99), and high burden (100–150) (Tran et al., 2014).*Kidney Disease Quality of Life (KDQOL™) questionnaire:* The KDQOL-36^TM^ consists of five dimensions: Physical Component Summary (PCS), Mental Component Summary (MCS), Burdens of Kidney Disease (BKD), Symptoms and Problems of Kidney Disease (SPKD), and Effects of Kidney Disease (EKD). Numeric items are transformed into a 0–100 points scale, with total possible scores ranging from 0 to 3600 (higher scores indicate better quality of life) (Hays et al., 1994).*Adherence to Refills and Medications Scale (ARMS):* This is a 12-item medication adherence assessment tool with proven reliability and validity that was developed in English language and translated into several languages including Turkish,(Gökdoğan & Kes, 2017) Korean,(Kim et al., 2016) Chinese,(Chen et al., 2020) Polish,(Lomper et al., 2018) and Arabic.(Alammari et al., 2021; Zidan et al., 2018) The total scores range from 12 to 48, with higher scores indicating poor adherence (Kripalani et al., 2009).

### Data management and analysis plan

#### Sample size

Assuming normally distributed outcomes, comparing post-randomisation main outcomes between two groups, the number of subjects per group for a two-sided significance level (α) of 5% and power (1 – β) of 90% is 106. Considering the proportion of PIM (primary outcome) use among CKD patients is 40%, based on previously published studies (Tesfaye et al., 2017). Assuming a target decrease of 50% in the proportion of PIMs in the intervention group compared to the control group (Kua et al., 2019), a total of 212 participants (106 from each group) is needed. To account for a 10% dropout rate, a total of 250 participants will be needed, with 125 participants per group (Naing et al., 2022). While the initial calculation assumed a dropout rate of up to 50%, findings from the pilot study demonstrated that the actual dropout rate did not exceed 10%, supporting the feasibility of the adjusted sample size.

#### Statistical analysis plan

Data will be analyzed using SPSS® version 29. The statistical analysis will be based on the intention-to-treat principle (i.e. all available data of the recruited participants will be included in the analysis according to their allocated arms, including missing items due to withdrawal, death, or non-response). Data will be analyzed using both descriptive and inferential analyses. Continuous variables will be reported as median, mean, and standard deviation (SD), interquartile range (IQR), while categorical variables will be presented as frequencies and percentages. We will examine the descriptive statistics of costs, including mean, SD, minimum, and maximum, to detect any potential outliers prior to conducting a statistical comparison. Student *t*-test and Mann−Whitney *U*-test will be used for comparison of normally distributed and non-normally distributed variables, respectively.

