### Economic analysis plan

This will be performed from the perspective of the healthcare provider (i.e. HMC). The benefit-to-cost ratio (sum of cost savings and cost avoidance)/ (operational cost of the deprescribing plan), and the net benefit (sum of cost savings and cost avoidance) – (operational cost of the deprescribing plan) will be calculated.
The total economic benefit of the deprescribing intervention will be calculated as the sum of the cost-savings resulting from medications use, and the cost avoidance associated with the intervention programme compared to usual care. Cost-savings based on the intervention will be the reduced cost of therapy associated with the reduction in utilisation (DDDs) of the targeted drugs, compared to the usual care. Cost avoidance will be the cost avoided by reducing ED visits and hospitalisations as unintended consequences of the polypharmacy use of medications.The cost of the programme will be represented by the operational cost of running the deprescribing intervention plan. The costs will include commonly considered non-protocol-driven resources that are strictly utilised under the different stages of the intervention plan workflow, including development and implementation. Also, the cost of the programme is any increase in the cost of medication use, hospitalisation, and ED visits, if any, compared to the usual care. Only direct medical costs will be considered in calculating the monetary value of the benefit associated with drug use, hospitalisation, and emergency admissions.

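### The t-test/Mann-Whitney rule contradicts the adjusted regression set out later, and would attach to costs a p-value that does not concern mean cost

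*Protocol article*

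**What the plan says.** All places are in the protocol article.

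- **Statistical analysis plan.** Descriptive statistics of costs are examined "to detect any potential outliers prior to conducting a statistical comparison". The next sentence says that Student's t-test and the Mann-Whitney test "will be used for comparison of normally distributed and non-normally distributed variables, respectively". It mentions no covariates and does not confine the tests to baseline tables or description.
- **Covariates and subgroups.** All analyses adjust for the stratification variable, gender, comorbidities and age. The primary and relevant secondary outcomes are also adjusted for baseline.
- **Multiple testing.** Unadjusted tests beside adjusted ones are foreseen, but only for the primary outcome.
- **Detailed analyses approach.** Secondary outcomes are analysed by ordinary least squares or Poisson regression. "For continuous outcomes, linear regression adjusted for baseline will be used without data transformations". Effects are mean differences in change, and every group difference carries a 95% confidence interval.
- **Secondary outcomes.** Cost-benefit and cost-savings are on the list.
- **Economic analysis plan.** The benefit-to-cost ratio and "the net benefit (sum of cost savings and cost avoidance) – (operational cost of the deprescribing plan) will be calculated". The section headed Sensitivity analysis adds one-way, multivariate and Monte Carlo analyses.

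**The concern.** There are two linked problems.

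First, the article gives two incompatible rules for the same comparisons. Under one, an analyst checks normality and runs an unadjusted test of means or ranks. Under the other, the analyst fits a covariate-adjusted regression on the untransformed scale. Two analysts could follow the text faithfully and report different p-values for quality of life, treatment burden, adherence or costs.

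Second, for costs the first rule can answer the wrong question. Deprescribing is meant to lower drug cost a little in many patients, which ranks pick up readily. An offsetting harm would appear as a few expensive admissions, which ranks barely register but which weigh heavily in the mean. A report could then call costs significantly lower when mean cost is equal or higher, and print that beside a net benefit built from totals.

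**Working it through.** **1. Do the rules conflict?**

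| Feature | Statistical analysis plan | Covariates and subgroups; Detailed analyses approach |
|---|---|---|
| Choice of method | by normality | fixed: linear or Poisson regression |
| Covariates | none | in all analyses |
| Baseline value | not used | adjusted for |
| Effect reported | none from Mann-Whitney on the mean scale | mean difference with 95% CI |

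Mann-Whitney gives neither a mean difference nor its confidence interval, so it cannot satisfy the right-hand column.

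**2. Group size for the illustration.** The plan has no figure for costs. Its only sample-size figure is for the primary outcome: "a total of 212 participants (106 from each group) is needed". With 40% against 20%, two-sided 5% and 90% power, the unpooled formula gives (1.960 + 1.282)² × (0.40×0.60 + 0.20×0.80) / 0.20² = 10.51 × 10 = 105.1, hence 106 per group. This reproduces the plan, and the point does not depend on it. The planned 125 per group less 10% dropout is 112.5, taken as 112.

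**3. Why ranks and means part company.** All cost inputs here are assumptions in arbitrary units. Control drug cost averages 1,000 (gamma, shape 4). An admission costs 15,000 on average (log-normal, log-SD 1). The intervention cuts drug cost by 30% and admissions are 22% against 20%.

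- Saving per patient: 0.30 × 1,000 = 300.
- Extra admission cost per patient: 0.02 × 15,000 = 300.
- Difference in true means: 0.
- Extra admitted patients in an arm of 112: 0.02 × 112 = 2.24.

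About two patients cancel a saving spread over all 112. The rank sum sees the 112 and hardly notices the two.

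**4. Simulated results, 112 per arm.** The third column is the share of trials in which Mann-Whitney gives p < 0.05 in favour of the intervention. Its nominal value is 2.5% when the distributions are identical.

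| Assumed setting | True mean difference | Favours intervention |
|---|---|---|
| Identical distributions | 0 | 2.2% |
| Drug cost −30%, admissions 22% vs 20% | 0 | 79% |
| Drug cost −20%, offset by admissions | 0 | 43% |
| Drug cost −15%, offset by admissions | 0 | 26% |
| Drug cost −10%, offset by admissions | 0 | 14% |
| Drug cost −30%, more variable (gamma shape 1) | 0 | 23% |
| Drug cost −30%, admissions 42% vs 40% | 0 | 32% |
| The same, gamma shape 1 | 0 | 9% |
| Drug cost −30%, admissions 24% vs 20% | 0.04 × 15,000 − 300 = +300 | 70% |

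A Welch comparison of means rejected in about 3% to 5% of trials in the equal-mean settings. In the 30%-saving settings with admissions of 24% and 22% against 20%, Mann-Whitney significantly favoured the intervention while the observed mean cost was higher with it in 34% and 33% of all trials.

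**5. A second set of assumptions, 106 per group, equal means, rejections in either direction.**

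- Drug cost 3,000 against 2,400, with admissions at 30% against 33% costing 20,000, so that 3,000 + 6,000 = 2,400 + 6,600 = 9,000: Mann-Whitney 22%, Welch 4.4%.
- Log-normal costs, log-SD 1.1 against 0.9: 29% and 5.0%.
- Log-normal costs, log-SD 1.2 against 0.8: 79% and 6.1%.
- Identical log-normal costs: 5.2% and 4.7%.

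**The case against.** The best defence is that the t-test/Mann-Whitney sentence is a general toolkit remark and the Detailed analyses approach is the governing text. That section already names an adjusted regression on the mean scale, and costs fall under it as a secondary outcome. This is a natural reading, but the article never says so. The only place that foresees unadjusted tests beside adjusted ones restricts them to the primary outcome.

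Three stronger inferences are tempting, and the objection to each is right.

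- **That Mann-Whitney is prescribed for costs.** It is not named for them. The link comes from the adjacent sentence and from the usual skewness of costs.
- **That expensive patients will be dropped.** The text speaks only of detecting outliers, and only for costs. Looking at minimum and maximum is ordinary data checking, and the same section keeps all available data by allocated arm. What remains is that no handling rule is stated.
- **That net benefit or the benefit-to-cost ratio is itself invalid.** Both are calculated directly from sums, with their uncertainty explored by Monte Carlo analysis. No p-value enters them.

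It is also fair that the largest simulated rates need a large, nearly uniform fall in drug cost offset by more admissions.

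**Conclusion.** The point holds as an unreconciled contradiction with a real consequence for costs. The unadjusted, normality-driven rule cannot stand beside the requirement for adjusted, untransformed regression with mean differences and confidence intervals. Followed as written, it would attach to right-skewed costs a p-value that does not refer to the arithmetic-mean difference underlying the economic result.

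The contradiction rests on the text alone. The size of the cost problem rests on assumed distributions. With equal true means, drug savings of 10% to 30% and slightly more admissions, Mann-Whitney falsely favoured the intervention in roughly 9% to 80% of trials against a nominal 2.5%. A reader might take the top of that range as a property of this trial. It is one corner of an assumed range.

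The matter should be corrected, but it is moderate: it touches continuous secondary outcomes and the inference on costs, not the primary outcome and not the calculation of net benefit or the ratio.

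**What to change.** 1. In the Statistical analysis plan, delete the t-test/Mann-Whitney rule for comparisons between arms, or restrict it expressly to description.
2. State that the adjusted regression in the Detailed analyses approach governs all continuous secondary outcomes.
3. Compare arithmetic mean costs by adjusted regression with an interval suited to skewed data, for example a bootstrap confidence interval or robust standard errors. If the bootstrap is chosen, its replicates can also be carried through to net benefit, alongside the planned Monte Carlo analysis.
4. State that the outlier check on costs is for data errors only and that verified extreme costs stay in the analysis.

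The cost is a few sentences and a short bootstrap run, with no new data. The drawback is wider cost intervals, which reflect how much the mean depends on a few admissions.
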